## Abstract

**Background:** New Zealand has relatively high rates of morbidity and mortality from infectious disease compared with other OECD countries, with infectious disease being more prevalent in children compared with others in the population. Consequences of infectious disease in children may have significant economic and social impact beyond the direct effects of the disease on the health of the child; including absence from school, transmission of infectious disease to other pupils, staff, and family members, and time off work for parents/guardians. Reduction of the transmission of infectious disease between children at schools could be an effective way of reducing the community incidence of infectious disease. Alcohol based no-rinse hand sanitisers provide an alternative hand cleaning technology, for which there is some evidence that they may be effective in achieving this. However, very few studies have investigated the effectiveness of hand sanitisers, and importantly, the potential wider economic implications of this intervention have not been established.

**Aims:** The primary objective of this trial is to establish if the provision of hand sanitisers in primary schools in the South Island of New Zealand, in addition to an education session on hand hygiene, reduces the incidence rate of absence episodes due to illness in children. In addition, the trial will establish the cost-effectiveness and conduct a cost-benefit analysis of the intervention in this setting.

**Methods/Design:** A cluster randomised controlled trial will be undertaken to establish the effectiveness and cost-effectiveness of hand sanitisers. Sixty-eight primary schools will be recruited from three regions in the South Island of New Zealand. The schools will be randomised, within region, to receive hand sanitisers and an education session on hand hygiene, or an education session on hand hygiene alone. Fifty pupils from each school in years 1 to 6 (generally aged from 5 to 11 years) will be randomly selected for detailed follow-up about their illness absences, providing a total of 3400 pupils. In addition, absence information will be collected on all children from the school rolls. Investigators not involved in the running of the trial, outcome assessors, and the statistician will be blinded to the group allocation until the analysis is completed.

**Trial registration:** ACTRN12609000478213

## Background

New Zealand (NZ) has relatively high rates of morbidity and mortality from infectious disease compared with other OECD countries, with infectious diseases, predominantly acute respiratory infections, accounting for 12% of admissions to NZ hospitals [1]. Children, the elderly, and socially disadvantaged groups are known to

be at higher risk of infectious disease than others in the population.

One of the important consequences of illness in school aged children is absence from school. Although short absences are unlikely to have any long term effect on children's learning, they are disruptive for the child, their family, and the class. However, infectious illnesses in school children have a number of effects in addition to the direct effects of the disease on the sick child's well-being. Transmission from an infected child to other pupils, staff, and family members affects their wellbeing

\* Correspondence: [contact]

School of Public Health and Preventive Medicine, Monash University, Melbourne, Australia

and may require time off school or work for those affected. In addition, when a child needs to stay at home because of illness, caregivers who are in paid work may need to take time off work or pay for care of the child at home. Therefore, childhood infectious diseases may have a significant economic and social impact on the community. However, this has not been well measured.

Reduction of infectious disease requires interruption of person to person transmission. The opportunities for transmission of infectious diseases offered by the school environment are likely to be an important contributor to the rates of infectious illness experienced by children. Given that it is not feasible to require all infectious children to stay away from school (because of asymptomatic transmission, high incidence, and often mild symptoms), reduction of transmission between children at school could be an effective way of reducing the incidence of infectious disease. A 2002 review concluded that "the weight of evidence suggests that personal and environmental hygiene reduces the spread of infection" [2]. There are a number of studies that have assessed the impact of improving hand hygiene to reduce infectious disease incidence in homes [3-6], childcare centres [7,8], University halls of residence [9], and primary schools [10-13]. Meta-analyses have found that handwashing reduces diarrhoea by approximately one third [14,15] and respiratory infection by approximately 20% [14,16].

A recent randomised controlled trial in China [10] found a 42% reduction ( $p = 0.03$ ) in school absence among children attending schools that were given a handwashing promotion programme and supplied with soap. In developed countries, soap, water, and drying facilities are frequently provided in schools; compliance with hand washing and drying has not been reported but is likely to be poor based on observational studies of older students [17].

Alcohol-based no-rinse hand sanitiser is an alternative hand cleaning technology, which requires only the liquid and a dispenser, no drying facilities, and needs minimum maintenance (refilling the dispenser as required). A recent meta-analysis of hand hygiene interventions in a range of community settings found that hand sanitisers reduced the rate of gastrointestinal illness and of 'combined illnesses' (e.g. school absences), but that there were very few studies and further, definitive studies are still required [14]. Importantly, no information was provided on the potential cost-effectiveness of the intervention.

### **Trial objectives**

The primary objective of the trial is to establish if the provision of hand sanitisers in primary schools in the South Island of NZ, in addition to an education session on hand hygiene, reduces the incidence rate of absence episodes due to illness in children. Secondary objectives

include whether hand sanitisers are effective in reducing the (i) incidence rate of respiratory illness absence episodes, (ii) incidence rate of gastrointestinal illness absence episodes, (iii) average length of illness episode, (iv) incidence rate of absence for any reason, (v) average length of absence episode, (vi) average number of household members who become ill within one week of the participating child's illness onset. We will examine if the intervention is associated with any skin reactions. We will also undertake a cost-effectiveness analysis, providing incremental cost-effectiveness ratios for the cost per absence episode due to illness avoided, the cost per absence attributable to illness, and the cost per days of work lost for parents/guardians (hereafter referred to as parents). We will also conduct a cost-benefit analysis, with the benefits being measured using parents' reported willingness-to-pay (WTP).

## **Methods/Design**

### **Trial design**

The design of the trial will be a cluster randomised controlled trial (C-RCT). While this design is less efficient compared to an individually RCT, and will therefore require more children, it has been chosen for several reasons. This design will reduce contamination which would be likely to occur if students within the same school were allocated to both the hand sanitiser and standard hand washing interventions. Second, this design evaluates the effectiveness of how the intervention would be implemented in practice; with hand sanitisers installed in schools. The effectiveness of the intervention may vary if only some children within schools used the hand sanitiser compared to all children, because of the communicable nature of infectious diseases ('herd-effect'). Finally, it is more feasible to run the trial as a cluster trial since it involves less work for the teachers. As a C-RCT, teachers do not have to monitor which children use the hand sanitisers, as they would in an individually RCT.

A random selection of 50 children per school will be selected for whom detailed information about their illness absences will be sought from their parents. These children are referred hereafter as the 'follow-up children'. In addition to the 'follow-up children', absence information will be collected on all children, from the school rolls (Figure 1).

### **Eligibility and recruitment**

#### **Recruitment of schools**

A list of all primary schools will be obtained from the NZ Ministry of Education in September 2008. This list will include the total school roll size. Where the school has pupils in years 7 and 8, the school will be contacted to find out the number of pupils in years 1 to 6. Principals of all primary schools in Christchurch City, Dunedin City,

[figure not shown]

and Invercargill City Local Authority Areas, with greater than 100 children in years 1 to 6, will be approached by letter during the last term of 2008, asked to confirm that they currently have at least 100 year 1 to 6 pupils, invited to participate, and asked to respond on a 'fax back' form. Study staff will explain the study procedures further by telephone or in person, as requested. Schools that do not return their fax back form will be contacted by telephone to ask them to do so.

We will follow each school's usual procedures for deciding whether the school will be part of the study. For example, this may involve the principal gaining approval from the Board of Trustees; a group of elected people who are responsible for the governance, control, and management of the school. Based on recent experience from a study of gastrointestinal illness involving NZ primary schools, we estimate that approximately 50% of schools will agree to participate (*[name], personal communication*).

#### **Recruitment of follow-up children**

In each school, 50 children will be randomly selected from the school roll in February 2009 by a school liaison research assistant. For each school, a list of numbers between 1 and the total number of children in years 1 to 6 in that school will be randomly sorted. The school liaison research assistant will know what intervention group the school has been assigned to, but will be provided only with the first 50 numbers from the randomly sorted list and a printout of the current school roll by the school administrative staff. They will number the children on the list from 1 to the maximum number, and identify the children whose numbers correspond with the random numbers they have been provided with. They will record the name and class number of those children. The selected children's parents will be contacted by a letter and information sheet sent home via their child, to seek consent for follow-up, should those children be absent from school during terms 2 and 3.

#### **Inclusion criteria**

Schools will be included if the following criteria are met:

- 1) There are at least 100 children of primary school age (school years 1 to 6; children will generally range in age from five to eleven years) at November 2008.
- 2) Schools are currently not using hand sanitiser products or are willing to not use hand sanitiser products for the period of the trial if they are randomised to the control group.
- 3) Schools are within the city boundaries of Christchurch, Dunedin, or Invercargill in NZ.
- 4) The principal of the school provides written consent for the school to participate in the trial, be randomised, and potentially receive the hand sanitisers.

Follow-up children will be included if the following criteria are met:

- 1) Their parents are able to read and understand spoken English to a level where they can read the study information sheet, complete the consent form, and respond to telephone interviews. This will be assessed from a question on the consent form.

- 2) They attend a year 1 to 6 class in one of the included schools, at the beginning of the second school term in 2009 (the end of April).

#### **Exclusion criteria**

Schools will be excluded if they are a special needs school.

Follow-up children will be excluded if they meet the following criteria:

- 1) Their parents are principal investigators or study personnel of the trial.
- 2) The principal of the primary school directs us not to approach their family.

#### **Randomisation and allocation concealment**

Schools meeting the inclusion criteria will be randomly allocated, within stratum, to receive either the intervention or control. Within each stratum, half the schools will be allocated to the intervention group, and half to the control group. Three strata will be defined by geographical area (Canterbury, Otago, and Southland). Geographical area has been chosen as a stratification variable since we believe this could be strongly predictive of infectious disease if, for example, a flu or gastrointestinal illness affected only selective areas. Consideration was also given to the inclusion of school roll size as a stratification variable since cluster size is fairly commonly used as a stratification variable [18], potentially predictive of absence due to illness, and easily measured. However, an analysis of absence data collected from 12 primary schools in Dunedin over 20 weeks in 2007 revealed no statistically, or clinically, significant association between roll size and absence rate.

Two common methods for implementing restricted randomisation are stratification and matched pairs designs. We have chosen to use stratification in preference to a matched pairs design since the latter design has important limitations. In this C-RCT there are a large number of clusters (68), potentially making it difficult to find matching variables which will form distinct pairs. In addition, if a school opts out of the trial, the entire stratum is removed, resulting in a loss of power [18]. Finally, we wish to be able to calculate estimates of intra-cluster correlation (ICC) for interpretation of the results in this study and for providing estimates for the design of future trials. While this calculation is straightforward when stratification is employed, it is more difficult to estimate when a matched pairs design is used. Certain assumptions, some of which are untestable, have to be assumed for a matched pairs design [19].

The trial statistician (JM) will implement the randomisation. She will only be provided with school codes and

district and will randomise the schools to either "A" or "B", so as to remain blinded to the group allocation. Stata/MP 10.1 for Windows [20] will be used to generate the random numbers. PP will randomly allocate "A" and "B" to the intervention and control, prior to receiving the allocation list. Randomisation of all the schools will be undertaken at one time.

#### **Blinding**

It is not possible to blind the children, school administrative staff, or the school liaison research assistants. However, the investigators not involved in the running of the trial (JM, RA, MP, CB), outcome assessors, and statistician (JM) will be blinded until the analysis is completed.

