**Table 1 Outcome measures**

| Outcome                                                                                               | Collected by                            | Timing of collection                                              | Source              |
|-------------------------------------------------------------------------------------------------------|-----------------------------------------|-------------------------------------------------------------------|---------------------|
| Primary outcome                                                                                |                                         |                                                                   |                     |
| Number of absence episodes due to any illness                                           | Telephone interview                     | 8 - 9 days after the date of the first day of absence from school | Parents of children |
| Secondary outcomes                                                                             |                                         |                                                                   |                     |
| 'Follow-up children'                                                                           |                                         |                                                                   |                     |
| Number of absence episodes due to respiratory illness                                                 | Telephone interview                     | 8 - 9 days after the date of the first day of absence from school | Parents of children |
| Number of absence episodes due to gastrointestinal illness                                            | Telephone interview                     | 8 - 9 days after the date of the first day of absence from school | Parents of children |
| Length of illness episode                                                                             | Telephone interview                     | 8 - 9 days after the date of the first day of absence from school | Parents of children |
| Length of absence episode                                                                             | Telephone interview                     | 8 - 9 days after the date of the first day of absence from school | Parents of children |

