| Number of household members who become ill within one week of the participating child's illness onset | Telephone interview                     | 8 - 9 days after the date of the first day of absence from school | Parents of children |
| All children                                                                                   |                                         |                                                                   |                     |
| Number of absence episodes for any reason                                                             | Liaison research assistant  | Weekly                                                            | School roll         |
| Length of absence episode                                                                             | Liaison research assistant  | Weekly                                                            | School roll         |
| Adverse events                                                                                 |                                         |                                                                   |                     |
| Skin reactions                                                                            | Telephone interview                     | Following the intervention period                                 | Parents of children |

 'Follow-up children' only.

 Parents will not be telephoned where it is clear that the child was not unwell (for example, on a holiday, attended a funeral, etc).

 Through contact with school staff or by extracting the data in person.

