#### **Effectiveness analyses**

##### **Analysis subsets**

The principal of intention-to-treat (ITT) is the appropriate strategy to be used in the primary analysis of the data in this C-RCT for two key reasons. It has the advantage of providing an unbiased estimate of intervention effect because it maintains the balance in prognostic factors between intervention groups, brought about through randomisation. In addition, it allows for non-compliance of hand sanitiser use, therefore providing an estimate of intervention effect which is more reflective of what would occur should the hand sanitisers be implemented in schools [24,25].

Requirements of an ideal ITT analysis include full compliance with the randomised intervention, no missing responses, and follow-up on all participants [24]. In a C-RCT, non-adherence to the intervention and loss to follow-up are more complex than in an individually RCT, since these can occur at multiple levels. In this trial, at the school level, schools in the intervention group may cease using the hand sanitisers while schools in the control group may commence using hand sanitisers, and in addition, schools may withdraw. At the level of the child, there will be non-adherence to the intervention, children may move schools, and parents of 'follow-up children' may withdraw.

We plan to implement procedures to maintain compliance and minimise loss to follow-up. While we expect there will be some attrition, we do not expect this to be large for the primary outcome, or the outcomes

collected on all children. For the former, if we are unable to contact the parents' of the 'follow-up children' to ascertain why they were absent, we may be able to determine the reason for the absence from the school administrative staff. For the latter, this data will be collected from the school roll where possible. Therefore, as our primary analysis, we plan to present a modified ITT analysis, where we will analyse participants as they have been randomised, regardless of the intervention they received, but will not impute missing data. As a second approach, we plan to identify potential predictors of missingness through modelling, and include these predictors in the primary analysis model.

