#### **Ethical review**

The New Zealand Multi-Region Health and Disability Ethics Committee provided approval for the trial on 13 March 2009 (MEC/09/01/005).

C-RCTs offer additional ethical complexity compared to individually randomised participant trials [32-34], particularly concerning informed consent of individuals. In this trial, the school principals will act as the "gatekeepers"; providing written consent for the school to participate in the trial, be randomised, and potentially receive the hand sanitisers. Parents of all children in the schools allocated to the hand sanitiser group will be contacted with an information sheet explaining the study and informed that hand sanitisers will be fitted in each classroom in their child's school. Parents will be informed that they can opt their child out of using the hand sanitiser at any stage throughout the trial. Parents of the randomly selected sub-sample of children (including children in the intervention and control groups) will be asked to provide written informed consent for the researchers to conduct post-absence interviews with them.

Anonymised data on absences from all children will be collected from the school rolls. Consent for this data collection will not be obtained from parents. Parents of the children in the intervention group will be informed that this data will be collected, through the information sheet described above. Parents of the children in the control group will not be informed of the anonymised data collection.

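### The unqualified statement that outcome assessors are blinded can hold only for the telephone interviewers; roll outcomes, staff-supplied reasons and intervention-arm parents' reports are not blinded

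*Protocol*

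**What the plan says.** - **Blinding** (Protocol): "It is not possible to blind the children, school administrative staff, or the school liaison research assistants". The next sentence says that the investigators not running the trial, the outcome assessors and the statistician "will be blinded until the analysis is completed". Outcome assessors are not defined, and parents appear in neither list.
- **Abstract** (Protocol) repeats the claim: "outcome assessors, and the statistician will be blinded to the group allocation until the analysis is completed".
- **Table 1**, primary outcome: parents report by telephone interview, "8 - 9 days after the date of the first day of absence from school".
- **Table 1**, all-children outcomes: episodes of absence for any reason and length of absence are collected weekly by the liaison research assistant, "Through contact with school staff or by extracting the data in person".
- **Table 1, footnote 2**: "Parents will not be telephoned where it is clear that the child was not unwell". A holiday and a funeral are given as examples, and the list is left open.
- **Analysis subsets**: if the parent cannot be contacted, "we may be able to determine the reason for the absence from the school administrative staff".
- **Ethical review**: "Parents of all children in the schools allocated to the hand sanitiser group will be contacted with an information sheet", which tells them that dispensers will be fitted in their child's school.

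**The concern.** The primary outcome counts absence episodes due to illness, so each absence has to be labelled as illness or not. The section on the primary outcome measure itself accepts that illness is hard to diagnose accurately through parent interviews. A blinded interviewer records the label faithfully, but the label comes from a parent who may know the arm, or from school staff who do know it. Some absences are never put to a parent at all.

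Two things are at stake. First, a reader of the Abstract is told that the trial has a protection which covers only part of its outcome data. Second, if borderline absences are labelled differently in the two arms, the difference enters the rate ratio directly and looks like an intervention effect, or hides one.

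**Working it through.** **1. Who supplies or collects each item, set against the Blinding section**

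| Item | Supplied or collected by | Blinding status in the protocol |
|---|---|---|
| Reason for absence, usual route | Parent, to a telephone interviewer | Nothing contradicts blinding of the interviewer; intervention-arm parents are told of the sanitisers; control parents' knowledge of their arm is not stated |
| Reason for absence, parent not reached | School administrative staff | Listed as impossible to blind |
| Decision that no call is needed | Nobody named | Absence records come from schools through liaison assistants; both staff groups are listed as impossible to blind |
| Any-reason episodes and length of absence, all children | Liaison research assistant | Listed as impossible to blind |

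The second and fourth rows conflict with an unqualified statement that outcome assessors are blinded. The first is an omission: the source of the primary outcome is missing from the account of who is blinded. The third is a gap. The Data quality assurance section has the study co-ordinator check codes and dates, but gives nobody the exemption decision.

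**2. The plan's own sample size**

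Inputs from the Sample size section: control rate 2.2 and intervention rate 1.76 episodes per pupil over 20 weeks, ICC 0.15, 50 pupils per school, 80% power, 5% significance (two-sided, from Secondary analyses).

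- Pupils per arm before clustering: (1.960 + 0.842)² × (2.2 + 1.76) / (2.2 − 1.76)² = 160.5
- Design effect: 1 + 49 × 0.15 = 8.35
- Schools per arm: 160.5 × 8.35 / 50 = 26.8, so 27
- With 20% school attrition: 27 / 0.80 = 33.75, so 34

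The plan's 27 and 34 are reproduced. The issue is possible bias, not a wrong figure.

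**3. What differential labelling would do**

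The documents give no mislabelling rate, so q below is an assumption. Suppose there is no true effect, and a proportion q of intervention-arm illness episodes is labelled as not illness, over and above any such labelling in the control arm. The apparent rate ratio is then 1 − q.

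- q = 5%: 2.2 × 0.95 = 2.09, ratio 0.95, one quarter of the targeted 20% reduction
- q = 10%: 2.2 × 0.90 = 1.98, ratio 0.90, one half of it
- Same shift in the control arm instead: 2.2 / 2.09 = 1.05 and 2.2 / 1.98 = 1.11

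Using the sample-size variance, the standard error of the rate difference with k schools per arm is √[(rate₁ + rate₂) × 8.35 / (50k)]. For q = 5% and k = 27 this is √(4.29 × 8.35 / 1350) = 0.163, so the expected z is 0.11 / 0.163 = 0.675. The chance of a two-sided significant result is Φ(0.675 − 1.960) + Φ(−0.675 − 1.960) = 10.4%.

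| Assumed q | Null rate ratio | False-positive rate, 27 schools per arm | 34 schools per arm |
|---|---|---|---|
| 2% | 0.98 | 5.8% | 6.0% |
| 5% | 0.95 | 10.4% | 11.8% |
| 10% | 0.90 | 27.8% | 33.6% |

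**4. The staff fallback alone**

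If staff settle a share f of episodes and a proportion m of those is differentially mislabelled, the null ratio is 1 − f × m. With f from 5% to 30% and m from 10% to 30% (all assumed), it runs from 1 − 0.05 × 0.10 = 0.995 to 1 − 0.30 × 0.30 = 0.91.

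**The case against.** Visible classroom dispensers cannot be concealed, and the protocol openly says so. Several stronger readings are tempting, and the documents do not support them.

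- *That blinding of outcome assessors fails altogether.* The natural reading of the term is the telephone interviewers, and nothing says that they know the allocation. This stands: the fault is the missing qualification.
- *That an unblinded person screens out absences.* Footnote 2 names no one, and its examples are factual rather than borderline illness. What remains is that the list is open, no judge is named, and the records come from and through unblinded people.
- *That teachers label absences.* They are asked to oversee sanitiser use, but no section gives them a part in classifying absences.
- *That no check is free of the illness label.* Any-reason roll absence in all children is a planned secondary outcome and compares the same randomised schools. It is not stated for the follow-up children separately or tied to the primary result. The roll outcomes are collected unblinded but need no illness judgement, so the labelling concern does not carry over to them.
- *That the bias is 5–10% in favour of the sanitiser.* Those rates are assumed and applied to every intervention-arm episode, whereas the screen and the fallback touch only some. The direction is unknown. Both arms also receive the same hand-hygiene session apart from the sanitiser discussion.

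The statistical analysis plan is not shown and may already contain source flags or sensitivity analyses. Their absence from the protocol is therefore not an error; they are offered below as remedies.

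**Conclusion.** The point holds in a limited form. The Abstract and the Blinding section claim more than the design delivers: blinding at the point of assessment can hold for the telephone interviewers, but not for the roll outcomes or for staff-supplied reasons. It also does not make an intervention-arm parent's report a blinded one. The open exemption rule adds avoidable room for arm-dependent decisions.

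The size is unknown. Under an assumed one-directional excess of 5% to 10% across all intervention-arm episodes, the null rate ratio would be 0.95 to 0.90, and the false-positive rate about 10% to 28% with 27 schools per arm. The staff fallback alone would probably do less. These figures show sensitivity; they are not evidence that bias occurred. The matter should be corrected, but it does not invalidate the design.

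**What to change.** 1. **Correct the Abstract and the Blinding section.** Say that the telephone interviewers, the statistician and the investigators not running the trial are blinded; that parents, school staff and liaison assistants are not; and that the roll outcomes are collected unblinded. Cost: wording only.
2. **Replace footnote 2 with a closed list of roll reason codes** that exempt an absence from a call, applied by study staff with the arm masked, and call for every other absence. Cost: some extra calls for absences that prove not to be illness. This works only if in place during data collection, because calls never made cannot be recovered later.
3. **Record the source of each reason** (parent, school staff, screened out) and repeat the primary analysis with staff-supplied reasons handled differently, for example excluded, or all counted as illness in both arms. Do not count coded holidays or funerals as illness, since that would dilute any real effect. Cost: one data field and a repeat analysis.
4. **Report any-reason roll absence episodes in the follow-up children beside the primary result**, as supportive evidence free of the illness label. It should not override the primary result: any-reason absence includes non-illness absence, which could mask a genuine reduction in illness. The planned all-children outcome already partly serves this purpose. Cost: one extra analysis, provided that the roll records of the follow-up children can be identified.
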